### Stage 2: Presentation of Findings to Stakeholders

The research team will undertake preliminary data analysis, present these findings to community stakeholders, and engage them for assistance with interpretation and making of meaning. VE, CV, and HP have existing relationships with Māori health care providers, Hāpai Te Hauora, Well Women and Family, Sexual Wellbeing Aotearoa, and the Cancer Society New Zealand, who will all be warmly invited to participate meaningfully. Additional stakeholders may also be invited through the research team and stakeholder networks. It is likely that stage 2 will include a mix of in-person stakeholder *hui* (workshops) and *kanohi ki te kanohi* (face-to-face) meetings individually and in small groups.

*Whakawhanaungatanga* (building relationships) and *manaakitanga* (kindness and respect for others, emphasizing responsibility and reciprocity) will be prioritized throughout, using a flexible approach to best meet the needs, availability, and preferences of the stakeholders. The aim of the stakeholder engagement activities is to obtain feedback on the findings of stage 1 and to facilitate the co-designing of future research priorities. We anticipate that stakeholders will want to co-design in-depth focus groups and interviews with us; we will use the results of these focus groups and interviews as a foundation for further investigation. The focus groups and interviews are described in stage 3.

### Stage 3: Focus Group and Interview Guide and Pilot Focus Groups and Interviews

Based on the results of the survey and the stakeholders’ engagement, a research approach and focus group and interview guide will be developed and piloted with approximately 5 to 8 participants. The authors acknowledge this will require an amendment to existing ethics approval. The aim of stage 3 is not to reach qualitative data saturation but to confirm a research approach and focus group and interview guide for an in-depth qualitative study in the future. Focus groups and interviews will be offered in English and te reo Māori and will be audio-recorded and transcribed verbatim. Focus groups and interviews conducted in te reo Māori will undergo forward and backwards translation into English by a certified University of Auckland or University of Waikato translator. Interview participants will be sent copies of their interview transcript, and they will have 2 weeks to edit or add to the written version of the transcript.

### Data Analysis

The multiple forms of data obtained in stages 1 to 3, including the qualitative survey results, the interpretations and meaning developed with stakeholders, the focus group and interview guide, and the pilot focus group and interview transcripts, will be analyzed together using a collective, team approach to reflexive thematic analysis [28]. Analysis will use NVivo (version 14; Lumivero, LLC). The quantitative survey results will be analyzed using descriptive statistics generated in SPSS (version 30; IBM Corp).

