## Methods

### Overview

This multistage study aims to (1) better understand the relationship between social media and women’s sexual and reproductive health in Aotearoa New Zealand and (2) meaningfully engage with stakeholders and community groups to interpret the findings and propose solutions to identified problems.

This cross-sectional, mixed methods research will be conducted over 24 months in three stages: (1) online data collection, (2) presentation of findings to stakeholders, and (3) pilot focus groups and interviews. This paper addresses the primary stage of data collection (online data collection) and follows the Checklist for Reporting Results of Internet E-Surveys (CHERRIES) checklist [27].

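### The thematic analysis codes the interview guide and stakeholders' interpretations as data alongside women's own accounts; the guide should come out, and each theme should name its source

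*Protocol article*

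**What the plan says.** The Data Analysis section opens with "The multiple forms of data obtained in stages 1 to 3, including the qualitative survey results" and continues that "the interpretations and meaning developed with stakeholders, the focus group and interview guide, and the pilot focus group and interview transcripts, will be analyzed together", by a collective, team form of reflexive thematic analysis in NVivo. The quantitative survey results are handled separately, with descriptive statistics. The Methods part of the Abstract likewise applies thematic coding to every form of data it lists, with codes taken from the literature and from the data. Neither place distinguishes one type of source from another.

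The stage descriptions show where the later material comes from:

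- **Stage 2.** The team will analyze the survey, "present these findings to community stakeholders, and engage them for assistance with interpretation and making of meaning".
- **Stage 3, guide.** "Based on the results of the survey and the stakeholders’ engagement, a research approach and focus group and interview guide will be developed".
- **Stage 3, pilot.** The guide is then "piloted with approximately 5 to 8 participants". On purpose, the section says: "The aim of stage 3 is not to reach qualitative data saturation but to confirm a research approach", together with the guide, for a later in-depth study.

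The Introduction asks how women use social media for sexual and reproductive health information and support, and what advantages and disadvantages they see in it. The Overview gives two aims. The first is to understand that relationship; the second is to "meaningfully engage with stakeholders and community groups to interpret the findings and propose solutions to identified problems".

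**The concern.** The research question is about women's use and women's perceptions, so what answers it should be what women say. An interview guide holds questions, not answers. If it is coded with the transcripts, a topic that the guide's authors chose to ask about enters the material from which themes are drawn, whether or not any participant takes it up.

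The stakeholder material raises a milder form of the same problem. It belongs in the study, because the second aim calls for it, but it is comment on women's accounts by other parties. Those named as invited in Stage 2 are health care providers and health organizations. The Introduction reports that several groups of people in Aotearoa New Zealand are more likely to meet hostile or stigmatizing treatment from health services. It therefore matters to the reader whether a theme about access or stigma was voiced by women or offered by organizations. At stake is attribution: a finding presented as women's experience might rest partly on stakeholders' commentary or on the wording of an instrument.

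**Working it through.** No arithmetic applies. The plan gives no figure for this step and sets no code count, weight or threshold for a theme. The check is to take each pooled source and ask where it comes from and what it can show.

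| Source in the single analysis | Made from | A participant's account? | Can it show how women use social media? |
|---|---|---|---|
| Survey free text (Stage 1) | Answers to survey questions | Yes | Yes |
| Stakeholder interpretations (Stage 2) | Comment on the team's preliminary Stage 1 findings | No | Not directly; it serves the second aim |
| Focus group and interview guide (Stage 3) | Survey results plus stakeholder engagement | No | No; it is an instrument |
| Pilot transcripts (Stage 3) | New answers given while the guide is piloted | Yes | Yes |

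**Step 1: count.** Two of the four source types are participants' accounts and two are not. Of the three sources added after Stage 1, only the transcripts bring new accounts, from about 5 to 8 people.

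**Step 2: follow one idea.** Suppose, for illustration, that survey respondents write about embarrassment.

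1. The idea enters the corpus as survey text.
2. The team puts it in the preliminary findings, stakeholders comment on it, and the comment enters the corpus.
3. Survey results and comment shape the guide, so a question on embarrassment enters the corpus.
4. Pilot participants answer that question, and their answers enter the corpus.

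Items 2 and 3 add codable text but no new account from a woman. Item 4 does add one. That it was prompted does not disqualify it, since survey free text is prompted by questions too.

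**Step 3: look for a rule that keeps these apart.** The sections that describe the qualitative analysis are the Abstract, Stage 2, Stage 3 and Data Analysis. None says that interpretations or instruments are treated differently from accounts. Data Analysis says the opposite, by naming all of them as data and analyzing them as one body.

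**Step 4: look for a rule that turns recurrence into support.** There is none. Stage 3 sets out to confirm an approach and a guide, not themes. Survey Design says the survey gains value in conjunction with interviews of known participants, and Results Dissemination says the later stages will enhance understanding of the survey data. Neither passage says that a theme seen in several sources is thereby better supported.

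**The case against.** The strongest case for the plan is that reflexive thematic analysis is interpretive. It does not count codes or sources, so material that echoes earlier material does not inflate anything. Bringing stakeholders into the making of meaning is the second aim of the study, and the Discussion presents it as a strength. A condensed article also commonly leaves source labels in the coding software to a fuller document. And a reading of the survey alone will exist, because Stage 1 has its own preliminary analysis before stakeholders see it and early results are to be published.

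Most of this stands, and it rules out three stronger readings that a reader might infer:

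- **That the plan will treat recurrence across stages as corroboration.** No section says so. The sentence in Survey Design about conjunction with later stages responds to the lack of duplicate checks and strict access controls; it is not a rule for supporting themes. Counting how often one idea could be coded would matter only if the plan used frequency, and it does not say that it will.
- **That women's and stakeholders' contributions can no longer be separated.** Analyzing sources together does not erase their origin, and the separate Stage 1 analysis remains.
- **That the pilot transcripts are merely derived and should rank below the survey.** They are new first-person accounts, and interviewees may edit or add to their transcripts. The survey had no duplicate check and no attention checks, and four responses were identified as coming from a chatbot. It has no claim to rank above them.

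Nor should the guide be described as the team's work alone: stakeholder engagement feeds it, and stakeholders are expected to want to co-design the focus groups and interviews.

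What the objection does not answer is narrower. Placing the guide among the data is something the article states, not a detail that it leaves out. An instrument is not evidence about women's experience under any school of thematic analysis. And declaring stakeholder interpretation as a design choice does not by itself tell the reader which themes are women's and which are stakeholders'.

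**Conclusion.** The point holds in a limited form. The Data Analysis section enters an instrument and stakeholders' commentary into the same thematic analysis as women's accounts, with nothing stated to keep themes about women's experience resting on what women said. The consequence is a possible misattribution in the reported themes. It cannot be quantified and has not been shown to occur. Including the guide is the clearer fault; the stakeholder material needs identifying, not removing.

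This rests on three assumptions. The first is that the pilot participants will be women as the study defines them; Stage 3 says only participants. The second is that stakeholders speak as interpreters of findings and not as respondents. The article describes them that way, but it also allows further stakeholders to be invited, so the final group may be broader than the health organizations named. The third is that no fuller document already takes the guide out of the coded material. The change is a cheap improvement and not a flaw that undermines the study.

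**What to change.** Amend the Data Analysis section as follows, and bring the matching sentence in the Abstract into line:

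1. Remove the focus group and interview guide from the coded data. Report it as an output of Stages 1 and 2, or as context for reading the transcripts.
2. Build the themes that answer the research question from women's accounts, meaning both survey free text and pilot transcripts, with each coded extract tagged by source.
3. Keep stakeholder interpretation in the study, and identify it as such when reporting on the second aim.
4. State for each reported theme which source or sources it rests on.

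No new data are needed. The cost is source tags in NVivo, a little more coding and reporting, and a slightly less unified narrative. The Abstract schedules focus groups and interviews from August 2025, after survey collection closed in February 2025, so the rule is best fixed before pilot transcripts are coded.

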### Results Dissemination

The findings will be disseminated through academic conference presentations, peer-reviewed journal articles, summary reports to participants, detailed reports to stakeholders, and the University of Auckland and University of Waikato social media accounts. As the online portion of the study encompasses 1 of 3 stages, early results will be published with recognition that focus groups and interviews will significantly enhance the understanding of these initial data. Author SM is a medical illustrator and experienced graphic designer who will lead the social media dissemination. We anticipate that this will be completed with significant involvement from stakeholder groups. The results of this survey will be used to prioritize the focus of in-depth qualitative interviews and focus groups in stage 2, detailed above. Additional funding and ethical approval for this future research has been sought.

## Results

Ethical approval for the online survey was granted from the Auckland Health Research Ethics Committee on June 28, 2023, for 3 years, with amendments approved on July 1, 2024 (AH25633). The timeline of our research is presented in Table 1.

**Table 1 table1:** Timeline of our research.

Activity and outcomes			2023		2024				2025		
			October to December		January to June		July to December		January to June		July to December
**Stage 1**											
	AHREC^a^ amendment	✓		✓							
	Extend survey recruitment	✓		✓		✓					
**Stage 2**											
	Stakeholder engagement and *whakawhanaungatanga*^b,c^	✓		✓		✓		✓		✓	
	Analyze preliminary results			✓							
	*Hui* (workshops) with stakeholders			✓		✓				✓^d^	
	Submit papers 1, 2, and 3 for publication					✓					
**Stage 3**											
	Co-design study protocol and external funding applications					✓		✓			
	Apply to the Marsden Fund (NZ $360,000 [US $205,992])					✓		✓			
	Apply to the MBIE^e^ Endeavour Fund (NZ $1 million [US $572,200])							✓			
	Apply for HRC^f^ Project (NZ $1.2 million [US $686,640])									✓	
	Apply for Google Award for Inclusion (NZ $94,000 [US $53,787])							✓			

^a^AHREC: Auckland Health Research Ethics Committee.

^b^*Whakawhanaungatanga*: the process of building and maintaining relationships through shared connections, trust, and mutual respect.

^c^Ongoing throughout.

^d^After submission of funding applications, a celebratory *hui* will be held with all stakeholders and research partners.

^e^MBIE: Ministry of Business, Innovation & Employment.

^f^HRC: Health Research Council of New Zealand.

## Discussion

### Anticipated Findings

The Understanding Intimate Health in Online Spaces project aims to better understand the relationship between social media and women’s sexual and reproductive health in Aotearoa New Zealand. We anticipate (from early results [26]) finding that social media plays a significant role in allowing women to seek out information and care that they would otherwise struggle to access, and that this study can help inform clinical practice in community outreach.

A strength of the approach we have described is the meaningful involvement of stakeholders in the interpretation and meaning-making of the survey findings; in-depth interviews and focus groups provided input into the anticipated next phase of the research. This study takes a multidisciplinary approach bringing together researchers from a variety of disciplines, including public health, biostatistics, nursing, and public policy, as well as anthropology and the social sciences. The aim of doing so is to better understand from diverse perspectives how and if social media impacts some of the most intimate aspects of the health of marginalized groups in Aotearoa New Zealand, namely the sexual and reproductive health of women.

A limitation of our survey is that there were few methods used to assure the validity of participant responses. Responses that were clearly copied and pasted from an artificial intelligence tool were automatically excluded, but no questions were integrated as attention checks.

### Conclusions

The data analyzed to date support the multistage research design, which aims to use this internet survey–based research to launch more targeted in-person and in-community research methods to refine the data collected.

This study was conducted in one particular geographical and sociocultural context (that of Aotearoa New Zealand), and findings may therefore not always be generalizable to other contexts. However, the findings we expect to encounter align with the current literature on social media use and women’s sexual and reproductive health.

The methods used in this study are standard quantitative (survey) and qualitative (survey, focus groups, and interviews) research methods, and can be applied in a variety of contexts. Our study contributes novel insights into the role of social media as a tool for women to access sexual and reproductive health information and support, particularly when these women otherwise have limited access to these resources. Our research also highlights the importance of stakeholder engagement in knowledge production. This protocol provides a framework for investigating this topic in other, international contexts.

## Appendix

Multimedia Appendix 1 Survey.

Multimedia Appendix 2 CHERRIES checklist.

## Abbreviations

LGBTTQIA+: lesbian, gay, bisexual, transgender, takatāpui, queer/questioning, intersex, asexual/aromantic/agender, or another marginalized identity
STI: sexually transmitted infection
